## Replacement of individual subjects after withdrawal

Patients withdrawn because of problems with swallowing the FFM WLS primo pill, no measurement of TSBL, or those withdrawn for other reasons in the first 30 days will be replaced.

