# STUDY DESIGN

This is a double-blind randomized 5 year study with two arms. Patients who are scheduled for primary OLGB surgery are eligible when during the surgery total small bowel length can be measured and when they are able to swallow the Fitforme WLS primo multivitamin capsule. Patients will be allocated to one of the two surgical treatment arms by randomization at the beginning of the operation. Only the operating surgeon is aware of the allocation and will document total small bowel length, treatment allocation and BP-length in a coded database. Both the TSBL and the length of the BP-limb will not be documented in the patient file. The investigators and the patient will not be informed on the BP-limb length during the study.

Patients with a small bowel that could not be measured during surgery will be treated according to the current daily practice and will not enter the study.

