## Randomisation, blinding and treatment allocation

After informed consent is given, the patient is asked to swallow one Fitforme WSL primo capsule. A patient who is not able to swallow the capsule will be withdrawn form the study.

Randomization is performed using a table of random figures delivered by a independent party (clinical pharmacist), using envelopes with the treatment allocation.

The envelope contains a study number on the outside and the same number with one of the treatment arms within. The envelope will be opened by the OR nurse when the surgeon has succeeded in measuring the TSBL.

If the surgeon is not able to measure the TSBL the patient will be withdrawn from the study.

The study number and the patients medical file number will be forwarded to the principle investigator by the surgeon.

The surgeon will document the allocation, total small bowel length and length of the BP-limb in the file containing only study numbers. In the follow-up neither any of the usual care medical providers nor the patient is aware of the allocation or BP-limb length. The surgeon will not describe the TSBL and the BP-limb length in his surgical report.

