## Study procedures

A standard operation protocol for OLGB will be used in all patients. The pouch will be made with the help of a linear stapler. At first, the stomach will be transected horizontally at the junction of the corpus and antrum at the level of crow’s foot. A small pouch is made with help of a calibration sonde of 34 French, the pouch is finished near the angle of His. Then the total limb length is measured. With a succesfull TSBL measurement the OR nurse will open the envelop and the allocated procedure will be communicated to the surgeon. Based on the randomization outcome biliopancreatic limb length is measured. In case the measurement of the total limb length does not succeed, standard limb length of 150 cm is performed. An antecolic, retrogastric anastomosis is performed by liniar stapling and the remaining defect is closed by V-loc. An anti-reflux stitch is performed. Integrity of the anastomoses is checked by methylene-blue-test and in case of leakage, extra sutures will be applied. The mesenterial defect of Peterson will be closed as far as possible by endo hernia stapling or unresolvable V-loc.

The extra measurements of limb length will take less than ten minutes of time. In patients allocated to standard treatment the surgeon will construct a BP-limb of 150 cm. In patients allocated to the adjustment length, the length of the BP-limb will depend on the total small bowel length : < 500 cm : 150 BP; 500-700 cm : 180 BP and > 700 cm : 210 BP.

On leave of the hospital the patients will be provided with Fitforme WSL Primo multivitamin capsules for the following period and will be instructed to use one capsule once daily.

Follow-up will take place in accordance with usual care, i.e. after 1,6,12 and 24 months and yearly up till 5 years. Extra visits will be at 18,30,42 and 54 months for compliance check and distribution of FFM multivitamins.

Weight measurements and blood samples will be taken in accordance with the standard protocol of follow-up after bariatric surgery in our institute added with 20 ml for selenium and copper measurements and future lab tests at 1,3 and 5 years.

Data from 6,12 and 24 months and every year thereafter up to five years after surgery will be anonymously collected in a database.

At each visit standard care includes :

- inquiry after well being and complaints, side effects, adverse events
- documenting current medication use, both regular and over-the-counter, and when applicable CPAP use

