### Specific criteria for withdrawal

Patients who are not able to swallow the FFM WSL primo capsule and those in whom the surgeon cannot measure the TSBL will be withdrawn from the study and will be replaced.

Patients who develop complications during the first 30 days needing revisional surgery changing bowel length will be withdrawn from the study.

Patients who need a conversion from the OLGB to a RYGB during the study will be withdrawn from the study and not replaced. They will be analysed on a intention to treat principle and all data up to the conversion will be used in the study.

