## Follow-up of subjects withdrawn from treatment

Patients who are withdrawn from the study remain in usual care

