# STATISTICAL ANALYSIS

## Populations for analysis

## All efficacy analyses will be conducted using the full analysis set. The full analysis set will include all randomized patients with at least one post-baseline measurement and fulfilling all inclusion criteria, in accordance with the intention to treat principle (ITT).

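### Patients withdrawn within 30 days of surgery are replaced after allocation, so the 5-year efficacy comparison is not of the arms as randomised

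*Protocol*

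**What the plan says.** **Time of allocation.** Randomisation, blinding and treatment allocation (7.2) states: "The envelope will be opened by the OR nurse when the surgeon has succeeded in measuring the TSBL". Study procedures (7.3) agrees. Study design (section 3) instead places allocation "by randomization at the beginning of the operation".

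**Withdrawal and replacement.** Specific criteria for withdrawal (under 7.4) states: "Patients who develop complications during the first 30 days needing revisional surgery changing bowel length will be withdrawn from the study". That sentence does not mention replacement. Section 7.5 supplies it: besides capsule and measurement failures, "or those withdrawn for other reasons in the first 30 days will be replaced". For a later conversion to RYGB the criteria say the opposite. Those patients are not replaced, and "They will be analysed on a intention to treat principle and all data up to the conversion will be used in the study".

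**What follows withdrawal.** Section 7.6 says only: "Patients who are withdrawn from the study remain in usual care". Section 7.3 states: "Data from 6,12 and 24 months and every year thereafter up to five years after surgery will be anonymously collected in a database".

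**Analysis.** Populations for analysis (section 9) states: "The full analysis set will include all randomized patients with at least one post-baseline measurement and fulfilling all inclusion criteria", and describes this set as following intention to treat. Handling of missing data rules out imputation. The safety set is everyone randomised.

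**The concern.** Once the envelope is open, a withdrawal is an event after randomisation, and a revision that alters bowel length may be a consequence of the allocated operation. Replacing such a patient with someone who got through the first 30 days conditions the efficacy comparison on an early outcome. Randomisation then no longer guarantees that the compared groups are alike, and the intention-to-treat label does not describe what is compared.

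The rules also collide. A conversion to RYGB within the first 30 days must not be replaced under the withdrawal criteria, yet it falls within the replacement wording of 7.5. Site staff cannot follow both.

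An analysis plan cannot repair this afterwards, because a patient who was not followed has no 5-year weight to analyse.

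**Working it through.** **1. Following one patient through the rules.** The envelope is opened in theatre (7.2, 7.3). On, say, day 20 a complication leads to a revision that changes bowel length. The patient is withdrawn (7.4), replaced (7.5) and returned to usual care (7.6). The first listed study data point is 6 months (7.3), so the database would normally hold no post-baseline value and the patient fails the entry condition of the full analysis set. A 1-month visit with weight does exist in usual care. If that weight were counted, the patient could enter the set but would still have no 5-year %TWL, and only observed values are analysed. Either way the patient contributes nothing to the primary test.

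**2. The plan's own sample size (4.4).** Inputs: difference 5, SD 12 in both arms, two-sided alpha 0.05, t-test.
- Exact noncentral-t power is 0.798 at 91 per arm and 0.803 at 92. The stated 92 reproduces.
- With SD 12 and 9 at 92 per arm, power is 0.889, against the stated 88.8%.
- 92 + 14 = 106 per arm. The 15% allowance is for conversion only. After it, 106 × 0.85 = 90 are evaluable, with power 0.794.

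**3. Number affected.** The protocol gives no 30-day rate, so *w* = 1% to 5% is assumed.
- 106 × 0.01 = 1.1 and 106 × 0.05 = 5.3, so about 1 to 5 per arm.
- To end with 106 per arm under replacement, 106/(1 − *w*) = 108 (*w* = 1%) to 112 (*w* = 5%) must be randomised.

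**4. Possible bias.** Let *g* be the gap in mean %TWL between retained and removed patients (assumed, and the same in both arms). The mean of all randomised patients in an arm is the retained mean minus *w* × *g*. Analysing only retained patients and their replacements therefore overstates the difference by (*w* adjusted − *w* control) × *g*.

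| Removed: control / adjusted | *g* = 10 | *g* = 20 | *g* = 35 |
|---|---|---|---|
| 1% / 1% | 0 | 0 | 0 |
| 1% / 3% | 0.2 | 0.4 | 0.7 |
| 1% / 5% | 0.4 | 0.8 | 1.4 |
| 2% / 5% | 0.3 | 0.6 | 1.05 |

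Removal in one arm only, at 2% to 5% with *g* = 10, gives 0.2 to 0.5. Setting the control rate to zero instead of 1% adds 0.01 × *g*, at most 0.35. A gap of 35 means that removed patients would have lost almost no weight. If more patients were removed from the control arm, the sign would reverse.

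**5. Cost of not replacing.** Suppose none of these patients yields a 5-year weight and 15% of the rest are lost. Then 106 × 0.99 × 0.85 = 89 per arm (power 0.789), down to 106 × 0.95 × 0.85 = 86 per arm (power 0.775). The reference is 0.794 from step 2.

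**The case against.** A reader might infer that early surgical failures vanish from the trial. The protocol does not support that. The safety set holds everyone randomised, and surgical complications within one month are shown separately. Withdrawals are tabulated by arm with time and reason, and possible bias from them is to be investigated. Operative complications are also reviewed after 50 and 100 operations (7.7). This objection stands in full and confines the point to efficacy and long-term follow-up.

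A reader might also infer that these patients can never enter the full analysis set. No sentence says that replaced patients are deleted, and the 1-month weight leaves a possible route. The exclusion is an inference from several rules. It is a strong one for the 5-year endpoint.

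A third tempting reading is that the unblinded surgeon could steer who is removed. Section 7.4 gives withdrawal to the patient or, for urgent medical reasons, to the investigator, and section 3 keeps both uninformed of limb length. Influence through the decision to revise is conceivable but undocumented.

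Finally, the size is modest. The standard error of the difference at 92 per arm is 12 × √(2/92) = 1.77 points, above every bias in the table. The protocol states that a longer limb carries no extra surgical risk, and both arms receive 150 cm when the bowel is shorter than 500 cm, so it offers no basis for expecting a marked imbalance. Nor does it show that removed patients would lose less weight. This limits the expected bias but does not reconcile the contradictory rules.

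**Conclusion.** The point holds for the efficacy comparison. Followed as written, the plan selects patients after randomisation. It contradicts its own intention-to-treat statement, and it treats an early revision and a conversion to RYGB by opposite rules that overlap in the first 30 days.

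About 1 to 5 of 106 patients per arm would be affected at an assumed 1-5%. Bias is zero if removal rates and outcomes are equal, and a few tenths of a %TWL point under moderate assumptions. It reaches about 1.4 points, against a target of 5, only if removal is 5% against 1% and removed patients lose almost no weight. The rates and gaps are assumptions, not protocol figures. Planned power is not the problem, since replacement protects it.

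Replacing capsule and measurement failures is harmless, provided that allocation follows bowel measurement as 7.2 and 7.3 say. The different timing in section 3 leaves that open.

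**What to change.** - **7.4 and 7.5:** limit replacement to patients whose envelope was never opened (capsule test failed or bowel length not measured). After opening, do not replace anyone, and do not end study follow-up because of an early complication or revision. State one rule for a conversion to RYGB within 30 days.
- **Section 3:** make the time of randomisation agree with 7.2 and 7.3.
- **7.6:** seek weight to 5 years from every patient whose envelope was opened, unless the patient withdraws consent. The right in 7.4 to leave at any time is untouched.
- **Populations for analysis:** keep these patients in the full analysis set by allocated arm. Dropping the post-baseline condition alone would not change the primary test, because only observed values are used. The gain comes from the continued weight follow-up.

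The cost is protocol wording, some extra follow-up and a few patients per arm not replaced. Power is about 0.78-0.79 if none of them provides a 5-year weight, against 0.794 otherwise. Clinical management of the complications is unchanged.

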## Follow-up of subjects withdrawn from treatment

Patients who are withdrawn from the study remain in usual care

## Premature termination of the study

Reasons for prematurely termination of the study are :

an unexpectedly high rate of surgical complications due to measuring total small bowel length or adjusting the BP-limb length as to the discretion of the investigator.

An unacceptable percentage of complications like excessive weight loss, diarrhea or nutrient deficiencies in either study arms as to the discretion of the investigator .

This will be investigated, at first without unsealing treatment allocation after the first 50 and 100 operated patients (operative complications) and after 1 and 2 years after start of the study for non-operative complications. If there is a high complications rate in the whole group treatment allocation will be unsealed to investigate further.

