### Secondary study parameters/endpoints

1) Percent of total weight loss (%TWL) at 1,2,3,and 4 years.

2) Percent excess weight loss (%EWL) at 1,2,3, 4 and 5 years.

Definition: %EWL (Initial Weight – Postop Weight) / (Initial Weight – Ideal Weight)

(ideal weight is defined by the weight corresponding to a BMI of 25 kg/m2 )

3) Percent excess BMI loss (%EBMIL) at 1,2,3, 4 and 5 years.

Definition: %EBMIL (ΔBMI / (Initial BMI – 25)) * 100]

4) Proportion of patients with 22 ≤ BMI ≤ 30 Kg/m^2^ at 1,2,3, 4 and 5 years

5) Mean number of daily bowel movements in the last two weeks at 6 months, 1,2,3, 4 and 5 years.

6) Mean number of days with daily bowel movements > 3 in the last two weeks at 6 months, 1,2,3, 4 and 5 years.

6) Quality of life measured by the RAND-36 questionnaire at 6 months, 1,2,3, 4 and 5 years, absolute and compared to before surgery.

7) percentage of patients experiencing moderate to severe dumping symptoms defined by the Dumping Severity Score (DSS) at 6 months, 1,2,3, 4 and 5 years, absolute and compared to before surgery.

Moderate to severe is defined as 3 or more dumping symptoms with a severity score of 2 or 3 on a 4-point Likert scale. Symptoms are divided in two categories, e.g. early and late,

as described by Emous et.al. (7)

8) percentage of patients who have neither deficiencies of iron, nor vit. D, nor vit B12 without extra suppletion, at 6 months, 1,2,3, 4 and 5 years . Deficiencies are based on the local normal laboratory values.

9) Proportion of patients who have a deficiency at 6 months, 1,2,3, 4 and 5 years, or received extra suppletion for:

- iron (ferritin)

- vitamin B_12_

- vitamin D_3_

- Vitamin B_1_

- Vitamin B_6_

- Folic acid

- Vitamin A

- Vitamin D

- Calcium

- Phosphate

- Albumin

- Zinc

- Copper at 1,3 or 5 years

- Selenium at 1,3 or 5 years

10)Proportion of patients at 1,2,3, 4 and 5 years without diabetes, both with remission and without de novo, defined as an HbA1c less than 48 mmol/mol without diabetes medication in the last 6 months.

11)Proportion of patients at one year and two years with improvement of diabetes, defined as a reduction of HbA1c of 10mmol/mol or more but not reaching remission criteria and/or less anti-diabetic medication.

12)Proportion of patients at 1,2,3, 4 and 5 years with remission of hypertension, defined as a blood pressure of 140/90 mmHg or less without antihypertensive medication.

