## [Data Safety Monitoring Board (DSMB) / Safety Committee]

Based on the current experience of the surgeons with the procedures a DSMB is not

considered necessary

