## Interim analysis (if applicable)

The first interim analysis will be performed after 50 patients have been included in order to see whether the number of patients with a TSBL of < 500cm, allocated to the intervention, will not jeopardize the study power.

Interim analyses will be performed after all patients have completed the visits at 1,2,3 and 4 years. The deblinding of the allocated treatment will be performed by an independent person, who is not part of the investigation team

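### The scheduled termination review for non-operative harms stops 2 years after study start, so it covers no follow-up beyond 24 months, and the yearly interim analyses are not linked to it

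*Protocol*

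**What the plan says.** Section 7.7 (Premature termination of the study) gives two groups of reasons for stopping, both left to the investigator's discretion. The second is "An unacceptable percentage of complications like excessive weight loss, diarrhea or nutrient deficiencies in either study arms". Operative complications are checked by patient count, after the first 50 and the first 100 operations. The others are checked "after 1 and 2 years after start of the study for non-operative complications". The check is first made without opening the allocation, and then: "If there is a high complications rate in the whole group treatment allocation will be unsealed to investigate further". No later check is scheduled there.

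Follow-up is much longer. The Study Design section states: "This is a double-blind randomized 5 year study with two arms". Section 7.3 sets visits "after 1,6,12 and 24 months and yearly up till 5 years". The same harms are measured to the end, for example "Mean number of days with daily bowel movements > 3 in the last two weeks at 6 months, 1,2,3, 4 and 5 years", and deficiencies on the same schedule.

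Section 9.4 adds: "Interim analyses will be performed after all patients have completed the visits at 1,2,3 and 4 years", with unblinding by someone outside the investigation team. It does not mention the 7.7 criteria or a safety purpose for these analyses. Section 8.5 begins "Based on the current experience of the surgeons with the procedures a DSMB is not" and concludes that none is needed.

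**The concern.** Operative harm appears early, so counting operated patients is a sensible clock for it. Nutritional harm, diarrhea and excessive weight loss need time after surgery, so the informative clock is completed follow-up. Section 7.7 counts from study start instead, which mixes patients operated long ago with patients operated last week.

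The Protocol itself shows why follow-up time matters. Eligibility requires no pre-operative deficiency of vitamin B12, vitamin D or iron, so these deficiencies can only arise after surgery. The Introduction cites new deficiencies in 20% or more of patients over the first postoperative year, and reports more deficiencies with longer limbs. The adjusted arm receives a longer limb than the standard arm whenever total small bowel length is 500 cm or more.

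Two things are at stake. A low pooled rate at the first look may reflect short follow-up rather than safety. And because allocation and limb length are kept out of the patient file, the unsealing step in 7.7 is the stated route from a high complication rate to an investigation by arm. After year 2 nothing on the schedule prompts it.

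**Working it through.** **Inputs from the Protocol.** Looks at 12 and 24 months after study start (7.7). Planned follow-up of 60 months per patient (Study Design). Total of 212 patients (4.4): 92 × 0.15 = 13.8, rounded to 14; 92 + 14 = 106 per arm; 2 × 106 = 212. The Protocol gives no figure for the follow-up available at each look, so there is none to reproduce.

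**Step 1: the ceiling, with no assumption on recruitment.** Follow-up at a look L months after study start is at most L. At L = 12 essentially nobody has passed 12 months. At L = 24 essentially nobody has passed 24 months. The last scheduled look therefore sees at most 24 of 60 months, and no 3-, 4- or 5-year visit. If the wording meant each patient's own 1- and 2-year visits, the ceiling would still be 24 months.

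**Step 2: what the looks would contain.** The recruitment period is an assumption: even accrual over R = 1, 2, 3 or 4 years.

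- With at least 6 months at the 1-year look: 212 × 0.5/R
- With at least 12 months at the 2-year look: min(212, 212/R)
- Operated by the 2-year look: min(212, 212 × 2/R)
- Share of planned patient-time seen at the 2-year look: operated × mean follow-up in months / (212 × 60)

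| | R = 1 | R = 2 | R = 3 | R = 4 |
|---|---|---|---|---|
| 1-year look: with 6 months | 106 | 53 | 35 | 26 |
| 1-year look: with 12 months | 0 | 0 | 0 | 0 |
| 2-year look: operated | 212 | 212 | 141 | 106 |
| 2-year look: with 12 months | 212 | 106 | 71 | 53 |
| 2-year look: mean follow-up (months) | 18 | 12 | 12 | 12 |
| 2-year look: share of patient-time | 30% | 20% | 13% | 10% |
| Not yet operated at the 2-year look | 0 | 0 | 71 | 106 |

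**Step 3: when the Section 9.4 analyses fall.** They wait until all patients have completed a visit. The 1-year analysis therefore falls no earlier than R + 1 years after study start: 2, 3, 4 or 5 years. By then enrolment has been closed for a year, so these analyses cannot inform whether to operate on further patients.

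**Step 4: what a look based on follow-up would add.** A look when n patients have completed 12 months falls at 1 + nR/212 years.

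- n = 50: 1.24, 1.47, 1.71, 1.94 years
- n = 100: 1.47, 1.94, 2.42, 2.89 years

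For R of 2 or more, 212/R + n patients have been operated by then. With n = 50, 56, 91 or 109 are still to be operated for R = 2, 3 or 4. With n = 100, the numbers are 6, 41 or 59. For R = 1 enrolment is already closed. Every one of these dates is later than the existing 1-year look, so such a look should be added and should not replace it.

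**The case against.** The best defence is that the 1- and 2-year looks are planned checks, not the limit of oversight. The reasons for stopping carry no time limit and remain at the investigator's discretion. The suspension duty (Section 8), SAE reporting to the end of the study, the annual safety report and the annual progress report to the ethics committee all continue. Section 9.3 carries the non-serious forms of these harms as secondary endpoints, and Section 9.4 analyses data at 1 to 4 years. All of this stands. A reader might infer that harm emerging in years 3 to 5 would never be examined; the documents do not support that. What is missing is a scheduled assessment against the 7.7 criteria.

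A reader might also infer that the scheduled looks are empty. They are not: under the accrual assumed above, 26 to 106 patients have 6-month data at the first and 53 to 212 have 12-month data at the second. Nor does the Protocol show that excess harm first appears after year 2. Its one cited figure on timing concerns the first postoperative year, and measuring an outcome to year 5 is not evidence of late onset.

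The operation is done once, so stopping late cannot undo a limb already made, and deficiencies are substituted under standard care in any case. This limits what a late review can change. It does not remove its value while patients are still being enrolled, or for investigating a high rate by arm.

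Doing without a DSMB is a stated choice and does not by itself make the timing wrong. The reason given, surgical experience with the procedures, does not speak to nutritional harm.

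**Conclusion.** The point holds as a gap in scheduling. The only scheduled review against the non-operative stopping criteria cannot see beyond 24 of 60 months, whatever the recruitment rate and on either reading of the wording. On the plain reading, the first look has essentially no 12-month data and the second essentially no 24-month data.

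The patient counts rest on an assumed even accrual over 1 to 4 years. If recruitment finishes within 2 years, nobody is left to be operated at the last scheduled look and the gap concerns later follow-up only. At 3 or 4 years, 71 or 106 patients would be operated after it. The yearly analyses in Section 9.4 could cover follow-up through year 4, but nothing links them to Section 7.7. This should be corrected. It does not undermine the primary comparison, and it does not mean that later harms go unobserved.

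**What to change.** Amend Section 7.7 and reconcile it with Section 9.4:

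1. Keep the looks at 1 and 2 years after study start, and tabulate events and patient numbers by time since surgery, so that short follow-up is visible.
2. While enrolment is open, add a look when a stated number of patients have completed the 12-month visit. The sponsor should choose that number from the expected recruitment rate, using 1 + nR/212 to see when it falls.
3. State that the yearly analyses in Section 9.4, through year 4, are also assessed against the non-operative criteria of Section 7.7, and that they can trigger the unsealing step described there.

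The cost is about one paragraph and one or two extra tabulations; the yearly analyses are already planned. The change concerns the timing and linkage of reviews only. It sets no clinical threshold.

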## Sample size calculation

The null hypothesis in the study is as follows : the percentage TWL at five years in both groups is not different with a mean of 35. The alternative hypothesis is that the mean of the absolute difference in TWL in the experimental group is 5% more than the standard group (40% and 35% respectively).

For the evaluation of the primary endpoint of the percent total weight loss (%TWL) at five years, a sample size of 2x 92 will achieve 80% power to detect a (absolute) difference of -5.0% between the null hypothesis ( both group means of %TWL are 35.0) and the alternative hypothesis (mean of experimental group is a %TWL of 40.0) with estimated group standard deviations of 12.0 and 12.0 and with a significance level (alpha) of 0.05 using a two-sided two-sample t-test.

In case of a reduced standard deviation in the active treatment group of 9.0, the power achieved is 88.8%.

With an expected maximum drop-out due to conversion of OAGB to RYGB of 15% the sample size is 92 plus 14 = 106 patients in each group, leading to a total of 212 participants in the study.

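### Non-operative complications: the stopping reason is stated per arm, but allocation is unsealed only on a high pooled rate, which halves a one-arm excess

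*Protocol*

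**What the plan says.** The protocol's section Premature termination of the study gives two reasons to stop, both left to the investigator's discretion.

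- **Operative:** "an unexpectedly high rate of surgical complications due to measuring total small bowel length or adjusting the BP-limb length".
- **Non-operative:** "An unacceptable percentage of complications like excessive weight loss, diarrhea or nutrient deficiencies in either study arms".

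Only the second is worded per arm. The review is staged. It begins "at first without unsealing treatment allocation after the first 50 and 100 operated patients (operative complications"), and non-operative complications are reviewed "after 1 and 2 years after start of the study for non-operative complications". The next step is conditional: "If there is a high complications rate in the whole group treatment allocation will be unsealed to investigate further". No number is given for an unacceptable, unexpectedly high or high rate, and the section does not say who unseals.

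Other parts of the protocol bear on this:

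- The DSMB section says that a board is not "considered necessary".
- The interim analysis section plans analyses after all patients have completed the 1, 2, 3 and 4 year visits, and adds: "The deblinding of the allocated treatment will be performed by an independent person, who is not part of the investigation team".
- The Study Design section keeps the investigators unaware of limb length during the study.
- The sample size section plans "106 patients in each group, leading to a total of 212 participants in the study".

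**The concern.** A criterion about the rate in each arm cannot be read from a pooled rate. Because the arms are separated only after the pooled rate looks high, an unacceptable rate in one arm can be masked by an acceptable rate in the other.

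A one-arm excess is a recognised possibility here. The control arm receives 150 cm. The adjusted arm receives 180 or 210 cm unless total small bowel length (TSBL) is below 500 cm. The Introduction and the summary of clinical findings both report more deficiencies with longer biliopancreatic limbs in earlier series, and deficiencies are among the complications that the criterion names. At stake is how soon harm in one arm would be noticed in a five-year trial without a monitoring board. The primary efficacy analysis is not affected.

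**Working it through.** **1. The plan's own figures.** The termination section states no threshold, so the stopping rule has no figure to reproduce. The only planned number needed is the allocation: 92 + 14 = 106 per arm, 2 × 106 = 212. The underlying 92 per arm reproduces (5-point difference, SD 12, two-sided 5% t-test: power 80.3%). Allocation is therefore 1:1 by plan. The randomisation section describes no blocking, so the split at an early review is equal only on average.

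**2. Dilution.** Let p_S and p_A be the complication rates in the standard and adjusted arms. With equal arms:

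- pooled rate = (p_S + p_A)/2
- pooled excess over the standard arm = (p_A − p_S)/2

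The halving does not depend on the base rate. The documents give no complication rates, so the following are assumptions over a range:

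| Standard v adjusted | Pooled rate | Arm excess | Pooled excess |
|---|---|---|---|
| 5% v 15% | 10% | 10 points | 5 points |
| 10% v 20% | 15% | 10 points | 5 points |
| 10% v 30% | 20% | 20 points | 10 points |
| 20% v 40% | 30% | 20 points | 10 points |

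**3. Same threshold for pooled rate and arm.** Suppose 40% were the level regarded as high, the true rates are 20% v 40%, and 100 patients are reviewed. The pooled count reaches 40 of 100 with probability about 2%. The affected arm alone reaches 20 of 50 with probability about 55%. This is the starkest comparison, because it applies an arm-level threshold to a pooled rate.

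**4. Thresholds calibrated to the same false-alarm limit.** A fairer comparison lets the pooled threshold be lower. Each rule flags at r or more events, with r the smallest count that keeps false alarms at or below 5% when both arms have rate p_S. For N patients:

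- pooled false alarm: P(Bin(N, p_S) ≥ r); detection: P(Bin(N/2, p_S) + Bin(N/2, p_A) ≥ r)
- arm-level false alarm: P(Bin(N/2, p_S) ≥ r); detection in the affected arm: P(Bin(N/2, p_A) ≥ r)

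Watching two arms gives two chances of a false alarm. The last column therefore limits the chance that either arm flags, 1 − (1 − P(Bin(N/2, p_S) ≥ r))², to 5%. Example: 10 of 50 at a 10% rate has probability 2.45%, so 1 − (1 − 0.0245)² = 4.8%.

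| Rates | N | Pooled | One arm, ≤5% per arm | One arm, ≤5% for either arm |
|---|---|---|---|---|
| 5% v 15% | 100 | 10/100: 55% | 6/50: 78% | 7/50: 64% |
| 5% v 15% | 212 | 17/212: 86% | 10/106: 97% | 11/106: 94% |
| 10% v 20% | 100 | 16/100: 43% | 10/50: 56% | 10/50: 56% |
| 10% v 20% | 212 | 30/212: 67% | 17/106: 88% | 18/106: 81% |
| 20% v 40% | 100 | 28/100: 71% | 16/50: 90% | 17/50: 84% |
| 20% v 40% | 212 | 53/212: 96% | 29/106: 99.8% | 31/106: 99% |

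Each cell gives the flagging count and the chance of detection. The protocol does not say how many patients would have data at the 1- and 2-year reviews, so N = 100 and N = 212 are illustrations.

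**5. How many adjusted-arm patients differ from control.** The bowel-length study cited in the Introduction gives a median of 690 cm and an SD of 94 cm. Assuming normality, the share below 500 cm is Φ((500 − 690)/94) = Φ(−2.02), about 2%. The same study reports 2–3% below 400 cm, so the lower tail is heavier than normal and the true share is larger. On these figures most of the adjusted arm still receives a longer limb.

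**6. Timing of the deblinded analyses.** The first comes one year after the last patient's surgery, that is, one year plus the recruitment period after study start. It therefore falls after the 1-year safety review, and also after the 2-year review if recruitment takes more than a year. The recruitment period is not stated.

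**The case against.** The strongest defence is that looking first at pooled data protects the double blind, that the review is staged, and that a low enough pooled threshold would recover much of the sensitivity. This stands in part. The arms are compared once the gate is passed, and the calibrated comparison shows a moderate loss, far smaller than step 3 suggests. But no pooled threshold is stated, and the blind can be kept without a pooled gate because the protocol already has an independent person for deblinding.

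A reader might infer four stronger points that the documents do not support:

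- **That the 50- and 100-patient reviews fail in the same way.** They cover operative complications, whose stopping reason is not worded per arm. The bowel is measured in both arms, so a pooled rate suits that component. Only harm from adjusting the limb is diluted, and the protocol states that a longer limb does not raise surgical risk.
- **That this review is the only safeguard.** The sponsor must suspend the study if safety is jeopardised, SAEs go to the ethics committee within 7 or 15 days, and there are annual safety and progress reports. None of this reporting is stated to be by arm, and the safety analysis section treats non-serious weight loss, diarrhoea and deficiencies as secondary efficacy endpoints.
- **That nobody compares the arms unless the pooled rate is high.** The deblinded interim analyses take place regardless. They are late for this purpose and have no stated stopping role, so they soften the problem without curing it.
- **That the protocol expects harm in the adjusted arm.** Its aim is fewer deficiencies and bowel movements with adjustment. Excess harm is listed as a potential risk only.

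**Conclusion.** The concern holds for non-operative complications. The criterion is per arm and the gate is pooled, so a one-arm excess reaches the gate at half its size in expectation. That rests only on 1:1 allocation. The loss of detection depends on assumed rates, numbers and thresholds. With false alarms held to 5% for either arm, the pooled rule detects about 3 to 15 percentage points less often in the cases shown; with 5% per arm, about 4 to 23 points less. For operative complications the point is limited to harm from adjusting the limb.

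It would go too far to say that the review can never evaluate its criterion, since unsealing can follow. What the text supports is that the gate can miss the condition it is meant to find. This should be corrected, but it does not threaten the primary analysis.

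**What to change.** Reconcile the per-arm stopping reason with the pooled trigger in the section on premature termination:

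- At the reviews already planned at 1 and 2 years after study start, the independent person named under interim analysis tabulates the percentage with each non-operative complication in each coded arm, whatever the pooled rate.
- That person assesses each arm separately against the sponsor's own definition of unacceptable. Asking only whether the arms differ would not be enough, because two equally bad arms would pass.
- For this review only that person sees the allocation, and the investigator is told only whether the criterion is met in an arm.
- The same table may be added at the 50- and 100-patient reviews for complications attributed to limb adjustment.

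The clinical threshold remains the sponsor's decision. The cost is a short amendment and one more table per review, using a role and review dates that the protocol already has.
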